### Cost analysis

Ordinary least squares regression will be performed to quantify the cost of hospitalisation among preterms after adjusting for gender, GA, LOS, birth weight, OMT, time to first OMT, and DRG. Cost data is extracted from 2014 to 2015 administrative databases of the Regional Office of the Ministry of Health of Abruzzo where the NICU of the present RCT is located.

To calculate the precise cost, the reimbursement allocated to each DRG from the Istituto Superiore di Sanità (National Healthcare Institute) is used. Specifically DRGs and reimbursements considered are 386 (€12.932.69), 387 (€7.450.09) and 388 (€3.757.22) [25].

As for the study group, OMT costs are theoretically set at €20.00 considering fees from health insurance companies [26].

Cost estimates will be adjusted for inflation to 2014 euro value using the Medical Component of the Consumer Price Index.

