### Data entering and data export

Data will be collected using an *ad-hoc* platform already used in previous studies [13,20,21]. Medical records will be acquired daily by the NICU staff.

Osteopathic records will be reported once a week when the osteopathic service is provided.

Maternal data will be also include collecting the following information: type of delivery, foetal presentation, whether placental abruption, pregnancy complications, single versus multiple gestation, whether premature rupture of membranes and any other complication.

Neonatal data will be gathered using the following parameters: gender, GA, birth weight, infants small for GA, neonatal complications (diagnosed at birth and during hospitalisation), diagnosis-related group (DRG) at discharge and reasons for drop out, if any.

A monitoring board will be organised and periodically will review the safety of data according to survival rate at discharge and relative risk of developing any clinical complication. The group sequential method will be utilised to define the rate at which type I errors occur; the Lan-DeMets generalisation of the O’Brien-Fleming boundary will be chosen. Interim analyses will be performed. Moreover, the monitoring board will be in charge of data export.

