### Measures

The PIPP is a seven-item multidimensional (composite) measure of pain, largely used to assess acute pain in infants [11] and extensively validated for both preterm and term newborns [22]. Items are empirically and theoretically derived and are categorised as: contextual ((GA) and behavioural state (BS)), physiological (heart rate and oxygen saturation) and behavioural (facial actions). Numeric scores, reflecting baseline changes and based on an empirically 4-point scale (0, 1, 2, and 3), are provided for physiological and behavioural items. Conversely, the contextual items (GA and BS) have a reversed score (3, 2, 1, and 0) accounting for physiological differences related to prematurity. The maximum PIPP score is 21 for infants < 28 weeks GA and 18 for full-term newborns.

Considering LOS, according to international guidelines, well-determined discharge parameters are required and listed as follows: coordinated breathing, swallowing and sucking while feeding; stability of cardiorespiratory function; sustained weight gain and body heat at room temperature [23].

Regarding NICU costs, costs per day are calculated according to local authorities, multiplied by the days of hospitalisation. Costs are estimated in euros per day.

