## Discussion

The present single blinded RCT has been designed to explore potential advantages of OMT in the management of newborns’ pain. Currently, based on a patient-centred need-based approach, this research will be looking at the benefit of OMT rather than the efficacy of a specific technique or a pre-determined protocol. Moreover, it will attempt to confirm the effectiveness of OMT on LOS-shortening using a larger experimental study design and to corroborate the absence of placebo effects in newborns. Furthermore, it will explore potential differences between expert osteopaths and final-year students on the effectiveness of OMT.

To date, no osteopathic trial has been carried out in this field attempting to quantify the benefits of OMT in newborns’ pain using rigorous procedures and ‘gold-standard’ methods for clinical trials. This will be the first concrete experimental trial addressing this outcome. The expected advantages from the present trial will be reduction of pain, shorter LOS and lower neonatal costs in the OMT groups compared to sham and control groups.

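### The cost regression adjusts OMT for length of stay and discharge DRG, so its OMT coefficient cannot be the total effect on cost; time to first OMT is also undefined in two of the three arms

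*Protocol article*

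**What the plan says.** The relevant statements in the protocol article are these.

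- **Cost analysis, the model.** Hospitalisation cost is modelled by ordinary least squares "after adjusting for gender, GA, LOS, birth weight, OMT, time to first OMT, and DRG".
- **Measures, first cost definition.** For NICU costs, "costs per day are calculated according to local authorities, multiplied by the days of hospitalisation".
- **Cost analysis, second cost definition.** "To calculate the precise cost, the reimbursement allocated to each DRG" is used, with one fixed amount for each of DRGs 386, 387 and 388. For the study group, "OMT costs are theoretically set at €20.00"; no unit (per session or per infant) is given.
- **Data entering and data export.** The neonatal data include the "diagnosis-related group (DRG) at discharge".
- **Outcomes.** The mean differences between the three groups in LOS and in costs are both secondary outcomes.
- **Discussion.** The expected benefits include "shorter LOS and lower neonatal costs in the OMT groups compared to sham and control groups".
- **Abstract and Osteopathic procedure.** Only the study group receives OMT. The sham group has soft touch, and the control group has routine care alone.

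**The concern.** A between-arm cost comparison should capture everything that allocation does to cost, including what it does through a shorter stay. This model holds LOS fixed, although LOS is a trial outcome and the route by which the Discussion expects money to be saved. It also holds discharge DRG fixed, which under the second definition is the cost itself. In addition, it includes a variable that exists only for infants who received OMT.

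Cost is a named secondary outcome, and Methods/design gives cost-effectiveness as a secondary objective. If the OMT coefficient from this regression is reported as the effect of OMT on cost, a real saving could appear as no effect, or as a small added cost equal to the fee.

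**Working it through.** **Inputs.** The covariate list, both cost definitions, the three tariffs and the EUR 20 fee come from Measures and Cost analysis. The sample size of 40 per group, 120 in total, comes from Statistical analysis. The article states no numerical result for the cost analysis, so there is none to reproduce. Its sample size does reproduce: for a three-group ANOVA with f = 0.30 and alpha 0.05, power is 0.803 at 37 per group and 0.792 at 36.

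**1. Cost as daily rate times days.** Write cost = r × LOS, with r a common daily rate. Least squares fits this perfectly with coefficient r on LOS and 0 on every other term, including OMT. Now drop LOS and DRG (and time to first OMT, see step 5) and keep only baseline covariates. Because least squares is linear in the outcome, the OMT coefficient becomes r × d, where d is the adjusted LOS difference between arms. The planned model therefore removes exactly r × d, whatever r and d are.

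**2. Cost as DRG reimbursement.** Write cost = tariff(DRG). With DRG entered as categories, the DRG indicators fit cost perfectly and the OMT coefficient is again 0. This needs categorical entry. Reading the printed tariffs as EUR 12,932.69, 7,450.09 and 3,757.22, the steps are 12,932.69 − 7,450.09 = 5,482.60 and 7,450.09 − 3,757.22 = 3,692.87. They are unequal, so a linear term in the DRG number would leave a remainder and the coefficient would not be exactly zero.

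**3. Adding the OMT fee.** Cost becomes hospital cost + 20 × S, where S counts the fees charged and is 0 outside the OMT arm. By the same linearity, the OMT coefficient is the one obtained by regressing 20 × S alone on the covariates, and hospital cost contributes nothing. With one fee per infant and no time-to-first-OMT term, it is exactly +20. With a fee per session, it reflects the number of sessions. Either way only the fee is left.

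**4. Check by simulation.** The set-up was 40 infants per arm and 500 replicates per scenario, under both cost definitions. The assumed LOS effects were −2, −5 and −8 days; for per-day costing the assumed rates were EUR 300, 600 and 1,000. None of these values is in the article. Without the fee, the OMT coefficient was 0.0 (SD 0.0) in every scenario, with or without time to first OMT coded 0 in the other arms. This agrees with the algebra and does not depend on the assumed values.

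**5. Time to first OMT.** Infants with no value: 2 × 40 = 80 of 120.

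- *Complete cases.* The 40 OMT infants remain, and the OMT indicator equals 1 for all of them. The design has 9 columns (intercept, OMT, gender, gestational age, birth weight, LOS, time to first OMT, two DRG indicators) but rank 8, so the OMT effect is not identified.
- *A fill-in value c for sham and control.* The model runs, but the OMT coefficient is then the contrast for an OMT infant first treated at time c. If t is the coefficient on time, then b(c) = b(0) + c × t, so the estimate moves with an arbitrary choice whenever t is not zero.
- *Last observation carried forward,* the missing-data rule in Statistical analysis, cannot supply a value that never existed.

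**The case against.** The strongest defence is about scope. The Cost analysis section presents the regression as a way to quantify hospitalisation cost, with OMT as one of seven terms. It does not name the model as the estimator of the between-group cost difference in Outcomes, and Statistical analysis says separately that data will be analysed between the three groups. This stands in part: an unadjusted comparison of arm means remains available and is untouched. Still, this is the only model the Cost analysis section gives, and its OMT term invites reading as the cost effect. The linear regression in Statistical analysis compares OMT groups A and B, so it does not fill the gap.

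Second, cost may not be an exact function of LOS or DRG. The section draws cost data from 2014 and 2015 administrative databases and adjusts for inflation, and Measures mentions estimates in euros per day. Any such variation could move the coefficient off exact zero. That stands, but the coefficient would still condition on post-randomisation variables and would not be the total effect.

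Third, nothing in the article says that OMT can change an infant's DRG. If it cannot, the effect on DRG-based cost is the fee alone, and adjusting for DRG hides no saving. That also stands, so no DRG-based saving should be claimed.

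Fourth, the coding of time to first OMT may be left to an analysis plan that is not shown. Loss of both comparators therefore follows only under complete-case handling.

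**Conclusion.** The point holds for this regression. Its OMT coefficient cannot estimate the total effect of OMT on cost. It is zero or fee-only if cost is exactly a common daily rate times LOS, or a tariff with DRG entered as categories. In any other case it is a conditional effect that excludes whatever OMT saves by shortening stay. Including time to first OMT leaves the OMT term not estimable, or dependent on coding, because 80 of 120 infants have no value.

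A reader might infer that a false finding of no saving is built into the trial, or that both comparator arms will be lost. The article supports neither: arm means can still be compared, and complete-case handling is not specified. Nor does it support a euro figure for the hidden saving, since it gives no daily rate, no expected LOS difference and no link from OMT to DRG.

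Severity is should-fix. The outcome is secondary, and the primary PIPP analysis and the sample size are unaffected.

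**What to change.** 1. Reconcile Measures and Cost analysis to one prespecified cost definition for the between-arm comparison. The other may serve as a sensitivity analysis. Which definition leads is the investigators' choice; the Cost analysis section at present treats DRG reimbursement as the precise one.
2. Regress that cost, including OMT fees, on randomised arm (OMT, sham, control) plus baseline covariates only: gender, gestational age and birth weight. State the unit of the EUR 20 fee.
3. Remove LOS, DRG and time to first OMT from that model.
4. Confine any analysis of time to first OMT to the OMT arm, and label it descriptive.

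The cost is a change of analysis wording, with no new data and no additional infants.

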### Randomisation and masking

Patients will be randomly assigned in a 1:1:1 ratio to either the OMT, the sham or the control group (Figure 1). Newborns will be eligible for randomisation from the first day of life. Block randomisation will be performed according to a computer-generated randomisation list using a block size of nine, and stratified by OMT group.

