### Statistical analysis

According to Stevens *et al*. [11] the mean PIPP score for a painful procedure is 12.9 (standard deviation (SD), 3.4) and 6.0 (SD, 2.7) for a non-painful procedure. For a heel stick, the mean score is 10.3 (SD, 4.5) and 6.3 (SD, 3.2) for a simulated handling. However, as there is a lack of clinical trials in complementary medicine and/or manual disciplines, the sample size is computed considering an effect size (f) of 0.30, a statistical power of 0.80 and an α-level equal to 0.05 to produce a sample size of 37 per group. To prevent loss of power, the sample size is increased up to 40 subjects per group (total sample N = 120).

The primary analysis of the present clinical trial will be conducted according to per-protocol principle and intention-to-treat. Missing data will be handled using the last observation carried forward imputation technique. Arithmetic means and SD as well as median, percentage and range will be used to describe the general characteristics of the study population. Univariate statistical tests, Student’s *t*-test, analysis of variance (ANOVA) and chi square test, will be performed to compare the study groups and control group at the baseline. A linear mixed effect model will be used to evaluate the PIPP score across groups. Data will be analysed within and between the three study groups. Furthermore, a linear regression model will be applied to study the independent effect of OMT on primary and secondary endpoints between OMT groups A and B. Two-tailed *P*-values of less than 0.05 are considered to indicate statistical difference. To describe imbalances between groups, mean or relative risk with 95% CI will be used. Effect sizes will be computed stratifying by gestational age. R statistical programme (Vienna, Austria) will be used for data analysis [24].

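### The cost regression has no sham or arm term, so it does not give the listed three-group cost difference; read as 0/1, its OMT term pools sham with control

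*Protocol article*

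**What the plan says.** All references are to the protocol article.

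- **Allocation** (Randomisation and masking): "Patients will be randomly assigned in a 1:1:1 ratio to either the OMT, the sham or the control group". Here OMT names one arm, set against sham and control.
- **Cost outcomes** (Outcomes): the secondary outcomes include a mean difference in costs between the three groups and, separately, between the two OMT subgroups.
- **Cost model** (Cost analysis): an ordinary least squares regression quantifies hospitalisation cost "after adjusting for gender, GA, LOS, birth weight, OMT, time to first OMT, and DRG". No coding is given for OMT, and no sham, arm or subgroup term is listed.
- **Definition of cost**: under Measures, "costs per day are calculated according to local authorities, multiplied by the days of hospitalisation". Under Cost analysis, cost is the reimbursement attached to each of three DRG codes, with an OMT cost of €20.00 for the study group.
- **Other analysis statements** (Statistical analysis): "Data will be analysed within and between the three study groups", with neither cost nor a model named; and "a linear regression model will be applied to study the independent effect of OMT on primary and secondary endpoints between OMT groups A and B". The mixed model there is for the PIPP score, and the ANOVA and t-tests are for baseline comparisons.

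**The concern.** A three-group cost difference needs at least two treatment contrasts. The one regression whose terms are spelled out for cost carries treatment as a single item named after one arm. If that item is a 0/1 indicator, the model cannot separate sham from control.

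The sham arm is there to separate the effect of osteopathic treatment from that of being visited and touched. The Discussion expects lower costs than in both comparators and aims to corroborate the absence of placebo effects in newborns. Sham versus control is therefore an open question in this trial, and a pooled reference group assumes its answer. A reported cost saving for OMT would be hard to interpret, because it would not be the contrast with either comparator.

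**Working it through.** **1. The plan's own figure.** No figure is given for the cost model. The sample size rests on "an effect size (f) of 0.30, a statistical power of 0.80 and an α-level equal to 0.05 to produce a sample size of 37 per" arm. For a one-way ANOVA with k = 3 and noncentrality f² × N:

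- n = 36: 0.09 × 108 = 9.72, power 0.7916
- n = 37: 0.09 × 111 = 9.99, power 0.8035
- n = 40: 0.09 × 120 = 10.80, power 0.8359

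The stated 37 is reproduced. The trial was therefore sized as a comparison of three distinct groups.

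**2. What a 0/1 OMT term estimates.** Let mO, mS and mC be the mean costs in the OMT, sham and control arms, with 40 infants in each. Without other covariates:

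- coefficient = mO - (40·mS + 40·mC)/80 = mO - (mS + mC)/2
- = (mO - mS) + ½(mS - mC)
- = (mO - mC) - ½(mS - mC)

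Half of the sham effect is added relative to OMT versus sham, and half is removed relative to OMT versus control.

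**3. Numbers.** The documents give no cost effect, so these are assumed: mC = 10000, mS = 9000, mO = 8000.

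| Model | Result |
|---|---|
| 0/1 OMT term | 8000 - 9500 = -1500 |
| Three-level factor, sham versus control | -1000 |
| Three-level factor, OMT versus control | -2000 |
| Three-level factor, OMT versus sham | -2000 - (-1000) = -1000 |

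The single coefficient misses each OMT contrast by 500, which is half of the assumed sham effect. If the sham effect is zero, all three agree.

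**4. Why the other listed terms matter.** Take cost as day rate × LOS plus OMT fees. Assume €500 per day, €20 per session (that the fee applies per session is also assumed), about 8 sessions, and LOS shortened by 2 days under sham and 6 under OMT.

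- Without LOS in the model, OMT versus control is 500 × (-6) = -3000 and OMT versus sham is 500 × (-4) = -2000, both before fees. The pooled coefficient is about -2500 + 160 = -2340; the average over 500 simulated trials was about -2326.
- With LOS in the model, LOS explains everything except the fees. The OMT coefficient becomes about 20 × 8 = +160.

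The same holds if cost is the DRG reimbursement and DRG is entered as a factor: the tariff is fixed by the code, so only the fees (about +160) remain. A three-level arm factor placed beside LOS and DRG would also return little more than the fees. Time to first OMT has no value in 80 of the 120 infants. If they are dropped as missing, only OMT infants remain and a 0/1 OMT term cannot be estimated.

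**5. Price of the change.** With equal SD across arms, the variance factor for OMT versus sham is 1/40 + 1/40 = 0.0500, and against the pooled 80 it is 1/40 + 1/80 = 0.0375. The interval is √(0.0500/0.0375) = 1.155 times as wide.

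**The case against.** **The pooling is inferred.** The article gives short variable names without coding. DRG is also one word, yet it has three codes, so OMT could stand for the three-level group. Coding is often left to a full protocol or analysis plan. This stands in part, and the point is conditional on 0/1 coding for that reason. But the article does list the covariates, uses OMT elsewhere for one arm, and places it beside time to first OMT. The list as printed does not match its own outcome.

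**The regression may not be meant for the three-group outcome.** Its stated purpose is to quantify hospitalisation cost, and a general sentence promises analysis between the three groups. That is fair, but the sentence names neither cost nor a model, so nothing specific fills the gap.

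**Stronger readings.** A reader might infer three things that the documents do not support:

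- *That OMT is credited with half of any sham effect.* This holds only against OMT versus sham. Against OMT versus control, half is removed.
- *That OMT group A versus B cannot be compared on cost.* The Statistical analysis section already provides a linear regression for secondary endpoints between A and B, and cost is among them.
- *That false claims of a cost saving are inflated by a calculable amount.* Any such rate from a plain comparison of 40 with 80 infants does not describe the listed model, in which LOS and DRG absorb almost any arm effect.

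**Conclusion.** The point holds in a limited form. The cost regression as listed does not give the three-group cost difference named as a secondary outcome, and no other cost-specific model for it is named. If OMT is coded 0/1, which is the natural reading but is not stated, the unadjusted coefficient is OMT minus the mean of sham and control. It then lies half of any sham effect away from each contrast of interest, in opposite directions. The size in euros cannot be given, because the documents contain neither a sham effect on cost nor a cost SD; with no sham effect there is no distortion.

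The direction of any error depends on which comparison the reader has in mind, so this is a matter of an undefined estimate and not a demonstrated bias in favour of OMT. Recoding the treatment term is necessary but not sufficient: with LOS and DRG still in the model, the arm effects would be close to the treatment fees alone.

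**What to change.** In the Cost analysis section, state that for the between-group cost outcome:

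- randomised arm enters as a three-level factor (control, sham, OMT), with control as reference;
- OMT versus sham and OMT versus control are both reported with 95% CIs;
- this model omits LOS, DRG and time to first OMT; gender, GA and birth weight may stay, as they are fixed at birth.

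The longer covariate list can remain as a description of what drives cost, labelled as such and not as the treatment comparison. The A-versus-B cost comparison needs no change here.

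The change takes a few lines and no new data. Each pairwise interval is about 15% wider than one against the pooled 80 infants, assuming equal SDs.

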### Ethics

The approval of the Ethics Committee of the local health agency of Pescara (number 78/2013) has been obtained and the protocol has been registered on ClinicalTrials.gov (NCT02146677) on 20 May 2014. No disadvantages for the intervention are expected and no possible adverse events and side effects owing to OMT are predicted as confirmed by the recent osteopathic literature [13,15]. In any case, side effects and reason for drop out will be recorded during the research period and discussed in the final paper.

